### Analysis of the primary endpoint

The primary analysis plan will be based on a modified intent-to-treat design applied to participants who have received at least one dose of study medication. A two-sample log-rank test will be used to assess whether assignment to a 24-month course of NAC is superior to placebo for the primary composite endpoint (time to 10% relative decline in FVC, first respiratory hospitalization, lung transplantation, or death from any cause). Participants will be censored at 2 years of follow-up or at loss to follow-up, whichever occurs first.

Secondary analyses include assessing treatment differences in the composite endpoint graphically using Kaplan–Meier estimates. The effect of NAC versus placebo will be explored in subgroups of interest with results tabulated (estimated hazard ratio by subgroup, corresponding 95% confidence interval and p-value) as well as displayed via forest plots. Pre-specified subgroups include concomitant therapy usage, sex, race/ethnicity, smoking history, dichotomized age, dichotomized baseline FVC (L and % predicted), dichotomized baseline DLCO (ml/min/mm Hg and % predicted) and any respiratory hospitalizations in the previous year. Multivariable analyses of the primary endpoint will be conducted based on whether proportionality of hazards holds. Cox proportional hazards models will be used if the hazards are proportional, otherwise restricted mean regression will be used. Variables adjusted for in the multivariable model will include concomitant therapy (pirfenidone or nintedanib vs. none), age, sex, baseline FVC, and baseline DLCO. These variables are potential confounders and are commonly included in multivariable analyses of IPF studies. In addition, we will adjust for home spirometry participation if the participation of home spirometry is below 90% of randomized study participants. The adjusted hazards ratio, 95% confidence interval, and p-value will be used to assess the impact of NAC versus placebo on the primary composite endpoint from the multivariable model.

If there is more than 10% loss to-follow-up, sensitivity analyses will be performed based on multiple imputation of the primary outcome. If more than 10% of participants having missing adjustment variables for the secondary analyses of the primary endpoint, then sensitivity analyses multiply imputing the missing predictors will be performed. In the event more than 10% of participants switch concomitant therapy use after randomization (ex. participant who was not using pirfenidone at start of trial starts using pirfenidone mid-way through the trial), a sensitivity analyses will be performed that uses inverse weighting methodology.

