### Study overview

PRECISIONS is a multi-center, randomized, double-blind, placebo-controlled trial of 200 participants with TOLLIP rs3750920 TT genotype to receive NAC or placebo for a 24-month duration. The structure of the study is shown in Fig. 1. Study participants will be randomized to NAC or placebo in a 1:1 fashion, while receiving standard of care. Standard of care is defined as allowing background therapy with FDA-approved medications for IPF, such as pirfenidone or nintedanib, if taking a stable dose for at least 6 weeks prior to enrollment. Randomization will be stratified by stable concomitant IPF therapy use (pirfenidone or nintedanib) versus no pirfenidone or nintedanib use. A schematic overview of the study design is shown in Fig. 1.

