### Statistical analysis plan

Continuous variables will be summarized using descriptive statistics including, n, means, standard deviations, medians, 25th and 75th percentiles, and minimum and maximum. Categorical variables will be presented as counts and percentages. Demographic and baseline summaries will be provided by treatment group and overall. Two-sided hypotheses will be tested for endpoints at the 5% level. SAS software (SAS Institute, Inc., Cary, NC, USA) and R freeware will be used to perform the analyses.

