### Sample size and power calculation

It is anticipated that the event rate in the placebo arm will be highly dependent on the proportion of patients enrolled at different Gender, Age, and Physiology (GAP) scores [37]. The GAP index score will likely be heavily weighted towards 3 given the availability of pirfenidone and nintedanib. Assuming an exponential distribution for the composite endpoint comparable to that from the PANTHER study, we conservatively estimate a placebo yearly event rate to be 24% for the primary composite endpoint in participants not taking concomitant therapy [11]. We have also taken into account concomitant IPF therapy and conservatively estimate that 65% of the study population will be taking one of the two anti-fibrotic medications approved for treatment. We estimate the placebo event rate among participants taking concomitant IPF medications will be lower at a 12% yearly even rate. The estimate of the magnitude of the treatment effect is based on the PANTHER pharmaco-genetic study of the *TOLLIP* TT genotype, in which the primary endpoint was also a composite endpoint (decline of at least 10% in FVC, lung transplantation, hospitalization, and/or time to death) [13]. The hazard ratio was 0.14 in the PANTHER cohort and 0.23 in the validation cohort, both of which are large effect estimates. Given the retrospective and observational nature of this study, we took a very conservative approach in estimating the treatment effect. The estimate effect size for PRECISIONS is a 66.7% event reduction between NAC and placebo. Based on these estimates and a 10% dropout rate, we plan to enroll 200 randomized participants, which will provide 90.1% power assuming a two-sided type-I error rate of 0.05. Table 3 summarizes the power estimates for various event rates and treatment effects.

**Table 3 Tab3:** Statistical power assuming various event rates and treatment effects

Placebo event rate (%)	NAC event rate* (%)	Event rate reduction (%)	Power** (%)
24	6.0	75	97.5
30	7.5	75	99.3
36	9.0	75	99.8
24	8.0	66.7	90.1
30	10.0	66.7	96.0
36	12.0	66.7	98.7
24	12.0	50	62.3
30	15.0	50	73.1
36	18.0	50	80.6

*12-month event rates for the 35% of patients not taking concomitant IPF medication. The remaining 65% are assumed to have half the shown event rate in each arm based on taking IPF concomitant medication

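### Randomisation is stratified by antifibrotic use but the primary log-rank test is not, which leaves a valid but slightly conservative test and a small avoidable loss of power

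*Protocol article*

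**What the plan says.** Three parts of the protocol article bear on this point.

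- **Study overview.** Allocation is 1:1 and uses one stratification factor: "Randomization will be stratified by stable concomitant IPF therapy use (pirfenidone or nintedanib) versus no pirfenidone or nintedanib use".
- **Sample size and power calculation.** The factor is assumed to be strongly prognostic. For participants off antifibrotics, "we conservatively estimate a placebo yearly event rate to be 24% for the primary composite endpoint in participants not taking concomitant therapy". For those on them, "We estimate the placebo event rate among participants taking concomitant IPF medications will be lower at a 12% yearly even rate". The Table 3 footnote applies the same halving in both arms and puts 65% of participants in the on-antifibrotic stratum.
- **Analysis of the primary endpoint.** The primary test is given as "A two-sample log-rank test will be used to assess whether assignment to a 24-month course of NAC is superior to placebo", with no mention of strata. The factor appears only among the secondary analyses, as one of the prespecified subgroups and as a covariate: "Variables adjusted for in the multivariable model will include concomitant therapy (pirfenidone or nintedanib vs. none), age, sex, baseline FVC, and baseline DLCO".

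Testing is two-sided at 5%. The power statement is that "we plan to enroll 200 randomized participants, which will provide 90.1% power assuming a two-sided type-I error rate of 0.05", and the Table 3 notes say it rests on a log-rank test with exponential event times.

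**The concern.** Stratified allocation removes most of the chance imbalance between arms in a prognostic factor. The unstratified log-rank variance still allows for that imbalance as if it could occur, so the variance is too large for the design and the test rejects less often than its nominal level. The test also compares arms within risk sets that mix participants with quite different hazards, which dilutes the treatment contrast.

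What is at stake is efficiency and agreement between design and analysis. The trial takes the trouble to stratify, and the analysis that decides its result does not use the stratification. The loss is largest where the trial has least power to spare: Table 3 gives only 62.3% at a 50% reduction with the 24% placebo rate. Secondary time-to-event endpoints are to be analysed in a similar way, so the mismatch carries over to them.

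**Working it through.** **Inputs, all from the protocol article.** 200 randomised, 1:1; 35% off and 65% on antifibrotics (70 and 130 participants); yearly event rates at the design effect of 24% placebo and 8% NAC off antifibrotics, 12% and 4% on them; 10% dropout; 24 months of follow-up; two-sided 5%; exponential times.

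**Strength of the stratum effect.** The yearly hazard is −ln(1 − rate). For placebo this is −ln(0.76) = 0.274 off antifibrotics and −ln(0.88) = 0.128 on them, a ratio of about 2.1.

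**Expected events.** Two-year risk is 1 − (1 − rate)².

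- Placebo: 0.35 × 0.4224 + 0.65 × 0.2256 = 0.294.
- NAC: 0.35 × 0.1536 + 0.65 × 0.0784 = 0.105.
- With 10% contributing nothing, 90 per arm: 90 × (0.294 + 0.105) ≈ 36 events.
- Overall hazard ratio: ln(1 − 0.105)/ln(1 − 0.294) ≈ 0.32.

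**Reproducing the plan's power.** For this row, comparing two proportions with 90 per arm gives 89.6%. Freedman's formula gives 87.4% (N = 180) or 90.6% (N = 200), and Schoenfeld's 93.1% or 95.2%. A simulation of the unstratified log-rank (20,000 trials, allocation balanced within strata, 10% lost at baseline) gives 91.0%, against 90.1% stated. The same set-up gives 63.1% against 62.3% for the 24%/12% row, and 81.2% against 80.6% for the 36%/18% row. The plan's figures therefore fit an unstratified test.

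**Power with and without strata.** The article does not give the timing of dropout, so four models were tried (20,000 trials each). Cells show unstratified → stratified power, in %.

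| Dropout model | 24%/8% (design) | 24%/12% | 36%/18% |
|---|---|---|---|
| 10% lost at baseline | 91.0 → 91.7 | 63.1 → 64.8 | 81.2 → 83.0 |
| 10% lost, uniform over 2 years | 92.3 → 92.7 | 64.0 → 65.4 | 83.3 → 84.7 |
| Exponential, 10% over 2 years | 92.4 → 92.9 | 64.4 → 65.8 | 83.6 → 85.2 |
| Exponential, 10% per year | 90.9 → 91.5 | 62.8 → 64.1 | 81.6 → 83.3 |

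The gain is 0.4–0.7 points at the design effect. Over all runs it is about 1.2–1.8 points in the two 50%-reduction rows, with the top of that range in the 36%/18% row. From the squared ratio of mean test statistics, stratifying is worth roughly 3% of N at the design effect (0.03 × 200 = 6 participants) and about 6% in the 36%/18% row.

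**Type I error** (no treatment effect, 60,000 trials, 10% lost at baseline).

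| Placebo rate off antifibrotics | Unstratified | Stratified |
|---|---|---|
| 24% | 4.6% | 5.0% |
| 30% | 4.5% | 5.1% |
| 36% | 4.4% | 5.1% |

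The simulation error is about √(0.05 × 0.95/60,000) = 0.09 points, so the shortfall is real. Across other runs and dropout models the unstratified size was 4.2–4.6% and the stratified size 4.7–5.1%. Under simple randomisation the unstratified test has size 5.0%, so the conservatism comes from the stratified allocation.

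**Dependence on the prognostic gap.** With about 180 evaluable participants, the plan's 24%/12% split gave 90.5% → 91.1% power. With strata at 20%/15% it was 91.9% → 92.1%, and size was 5.0% against 5.1%. With equal rates of 16.2% (0.35 × 24 + 0.65 × 12), power was 90.6% for both tests.

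**The case against.** The strongest reply is that nothing here is wrong in the sense of invalid. The unstratified log-rank errs on the safe side, the power statement and the named test agree with each other, and the gain at the design effect is under one point. That gain also rests on a planning assumption: if antifibrotic use turns out to be weakly prognostic, it vanishes. The analysis of the primary endpoint does not ignore the factor either, since the multivariable model adjusts for it and the subgroup analysis examines it. Finally, this is a condensed article, and a fuller plan might apply strata.

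Most of this stands, and it limits the point to a minor one. Two parts do not remove it. The adjusted model is a secondary analysis that adds four further covariates and whose form depends on a check of proportional hazards, so it neither changes the primary p-value nor supplies a fixed test matched to the randomisation. And the article does not leave the test open: it names a two-sample log-rank, and a plan that used strata would disagree with that wording.

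A reader might infer that the trial is underpowered or that 90.1% is inflated. The documents do not support this, because the unstratified test delivers that figure. A reader might also infer a raised false-positive risk; the deviation is in the opposite direction.

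**Conclusion.** The mismatch is real and small. On the plan's own stratum rates, the primary test runs at about 4.2–4.6% instead of 5%. It gives up about 0.4–0.7 power points at the 66.7% reduction and about 1.2–1.8 points at a 50% reduction. It remains a valid test, and the stated power holds.

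It would be too strong to say that gains near two points apply at the design effect or arise from particular dropout patterns. All four dropout models gave under one point at the design effect, and the larger gains belong to the 50%-reduction rows.

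The size rests on three assumptions: that the 24%/12% prognostic gap is about right, that allocation is close to balanced within strata (the article does not give the method), and that event times are exponential as the plan states. A narrower gap reduces the benefit towards nil, but in the settings checked stratifying did no harm.

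**What to change.** In the primary analysis section, and in the statistical analysis plan, name the primary test as a log-rank stratified by antifibrotic use (yes/no) as recorded at randomisation. Report the hazard ratio and confidence interval from a Cox model stratified the same way. Keep the unstratified log-rank as a sensitivity analysis, and apply the same rule to the secondary time-to-event endpoints. Make the change before unblinding.

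The cost is a sentence or two of text. The stratum is already recorded for randomisation, two strata of about 70 and 130 participants are not sparse, and neither the endpoint nor the sample size changes.

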**Power estimates assume censorship/dropout rate of 10% for the NAC vs placebo comparison in 200 randomized participants. Calculations assume a 2-sided Type-I error rate of 0.05. Follow-up is planned to be 24 months for all patients. Power calculations were based on a log-rank test with assumed event rates following an exponential distribution

An interim sample size adjustment is also incorporated into the statistical analysis plan. Upon enrollment of at least 25 placebo participants with at least 12 months of follow-up, an interim sample size adjustment analysis will be performed. If the observed one-year event rate in this group of placebo participants is below 16%, the sample size will be increased by 40 participants to maintain at least 80% power for the study assuming a 66.7% event rate reduction in the NAC arm compared with placebo. No type I error would be spent as part of this analysis because the adjustment would not take into account the event rate in the NAC arm. This approach is a precaution that protects study power in the case of the placebo arm event rate being below the range anticipated in the design of the trial.

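### The primary log-rank test leaves out baseline severity, which the plan itself treats as prognostic; adjusting for covariates already listed could add a few points of power

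*Protocol article*

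**What the plan says.** - **Primary test** (Protocol article, Analysis of the primary endpoint): "A two-sample log-rank test will be used to assess whether assignment to a 24-month course of NAC is superior to placebo". No covariates and no strata are named.
- **Secondary model** (same section): "Variables adjusted for in the multivariable model will include concomitant therapy (pirfenidone or nintedanib vs. none), age, sex, baseline FVC, and baseline DLCO". It is a Cox model, or restricted mean regression if hazards are not proportional.
- **Prognosis** (Sample size and power calculation): the "event rate in the placebo arm will be highly dependent on the proportion of patients enrolled at different Gender, Age, and Physiology (GAP) scores". The next sentence adds: "The GAP index score will likely be heavily weighted towards 3 given the availability of pirfenidone and nintedanib". No hazard ratio per GAP point or stage is given.
- **Availability** (Procedures and Table 2): demographics, spirometry and DLCO are obtained by Visit 1, and Visit 1 assessments precede study drug.
- **Sizing** (Sample size and power calculation): "we plan to enroll 200 randomized participants, which will provide 90.1% power assuming a two-sided type-I error rate of 0.05". The note to Table 3 says the calculation used a log-rank test with exponential event times.

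**The concern.** The plan identifies baseline severity as prognostic, measures it before treatment and lists it for modelling, yet leaves it out of the one test that decides the trial. Two things follow when prognosis varies within arms. The unadjusted hazard ratio is pulled towards 1, and chance imbalance in severity adds noise that the primary p-value cannot remove. With about 38 expected events, both can matter. The adjusted result will be reported, but as a secondary analysis it cannot supply the confirmatory p-value. At stake is power that could be had without another patient, visit or measurement, in a trial where only about one patient in four has the required genotype.

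**Working it through.** **Inputs from the protocol.** 200 randomized 1:1; 24 months for all; 10% dropout; "Calculations assume a 2-sided Type-I error rate of 0.05". 35% not on antifibrotics, with yearly event rates of 24% (placebo) and 8% (NAC). 65% on antifibrotics, with half those rates (12% and 4%).

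**Step 1: reproduce 90.1%.** The 24-month event probability is the mixture of 1 − (1 − p)².

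- Placebo: 0.35 × 0.4224 + 0.65 × 0.2256 = 0.2945.
- NAC: 0.35 × 0.1536 + 0.65 × 0.0784 = 0.1047.
- Marginal hazard ratio: ln(1 − 0.1047) / ln(1 − 0.2945) = 0.317.
- Freedman formula, z = √D × (1 − HR)/(1 + HR) − 1.96. With 100 per arm, D = 39.9 and power is 90.6%. With exponential dropout, D = 38.0 and power is 89.2%.
- Two-proportion formula with 90 per arm: 89.6%.

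The stated figure is reproduced for the test it was computed for.

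**Step 2: what adjustment adds.** Assumption, because the protocol gives no figure: baseline covariates standing in for age, sex, FVC and DLCO have a combined log-hazard SD of s. Three simulation sets kept the plan's sample size, event rates, dropout and follow-up. Each compared the unadjusted log-rank with a Cox model adjusted for antifibrotic use and the covariates. Set A used the likelihood-ratio (LR) test with 6,000 trials per setting. Set B used Wald / LR with 10,000 trials (8,000 at the 50% reduction). Set C used Wald with 2,000 trials.

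Planned 66.7% reduction, power in %, log-rank vs adjusted:

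| s | Set A | Set B | Set C |
|---|---|---|---|
| none | 92.1 vs 92.3 | 92.9 vs 92.7 / 93.3 | – |
| 0.3 | – | 92.1 vs 92.3 / 92.9 | 92.1 vs 92.0 |
| 0.5 | 90.5 vs 92.2 | 91.3 vs 92.3 / 92.9 | 91.4 vs 92.6 |
| 0.75 (B) or 0.8 (A, C) | 87.6 vs 92.4 | 90.4 vs 93.4 / 94.0 | 90.0 vs 93.2 |

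50% reduction (24% vs 12%):

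| s | Set A | Set B | Set C |
|---|---|---|---|
| none | 63.6 vs 66.0 | 67.2 vs 67.2 / 68.7 | – |
| 0.3 | – | – | 67.2 vs 68.0 |
| 0.5 | 62.4 vs 66.6 | 63.7 vs 66.8 / 68.3 | 63.0 vs 65.9 |
| 0.75 (B) or 0.8 (A, C) | 57.5 vs 65.5 | 59.8 vs 65.3 / 66.6 | 59.2 vs 67.4 |

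**Step 3: how much is test size.** Under no treatment effect, the log-rank rejected in 4.8 to 4.9% of trials (set A) and 4.2 to 4.4% (set B, where it ignores the randomization stratum). Adjusted Cox rejected in 5.3 to 5.4% (A) and about 5.0 to 5.9% (B). A rough correction subtracts the gap seen with no prognostic effect:

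- Set A, 66.7% reduction (gap 0.2): 1.7 − 0.2 = 1.5 points at s = 0.5; 4.8 − 0.2 = 4.6 at 0.8.
- Set A, 50% reduction (gap 2.4): 4.2 − 2.4 = 1.8 at 0.5; 8.0 − 2.4 = 5.6 at 0.8.
- Set B Wald, 50% reduction (gap 0.0): 3.1 at 0.5 and 5.5 at 0.75, unchanged.

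**Step 4: a yardstick for s.** The one prognostic contrast the plan quantifies is 24% against 12%. The log hazard ratio is ln[ln(0.76)/ln(0.88)] = ln(0.274/0.128) = 0.76. With a 35/65 split the SD is 0.76 × √(0.35 × 0.65) = 0.36. An s of 0.5 or more therefore asks the four severity covariates together to be more prognostic than antifibrotic use is assumed to be.

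**The case against.** The strongest reply is that nothing here is wrong. A two-sample log-rank is a valid, pre-specified test in a randomized trial, and the trial was sized for it. The adjusted model is already planned with a fixed core of covariates, so the dispute is only about which analysis is called primary. The gain also rests on an SD the protocol does not give. GAP scores are expected to cluster near 3, and Table 1 excludes FVC below 45% predicted; both narrow the spread. Five covariates plus treatment on about 38 events is about six events per coefficient, and a primary Cox model would lose the plan's fallback for non-proportional hazards.

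Most of this stands, and it limits the point to efficiency at the lower end of the range. It does not remove the gain. The small-sample and proportional-hazards worries are arguments against a Cox Wald or likelihood-ratio test as primary. They are met by a score test of log-rank form calibrated by re-randomisation.

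Three stronger readings are tempting but unsupported:

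- That 90.1% is overstated or the trial underpowered. Step 1 reproduces it, and the simulated log-rank still has 90.5 to 91.4% power at s = 0.5.
- That the plan ranks GAP as the main driver of events. It says the rate depends strongly on GAP mix and ranks nothing.
- That a fixed loss of several points can be read off the plan. Every figure depends on s.

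**Conclusion.** The point holds as an efficiency improvement. At the planned effect, moving the listed covariates into the primary test is worth about 0 to 1 point of power at s = 0.3, 1 to 2 at 0.5, and 3 to 5 at 0.75 to 0.8. At a 50% reduction, where Table 3 itself gives only 62.3%, it is worth about 3 to 4 points at 0.5 (2.9 to 4.5 across the simulations) and 5 to 8 at 0.75 to 0.8. Part of the gain at the 50% reduction is test size (adjusted about 5 to 6%, log-rank 4 to 5%), so a calibrated test should be expected to give somewhat less. The direction is consistent from s = 0.5 upwards; at 0.3 and the planned effect the gain is close to nil. The restricted patient mix and the yardstick of 0.36 favour the lower end.

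**What to change.** Amend the analysis wording before unblinding:

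1. Take the primary p-value from a covariate-adjusted log-rank (score) test with antifibrotic use, age, sex, baseline FVC and baseline DLCO. Fix this list in advance, and keep the conditional home-spirometry covariate out of the primary test.
2. Calibrate the test by re-randomisation within the randomization strata, because only about 38 events are expected.
3. Report the adjusted hazard ratio and interval from the matching Cox model.
4. Keep the unadjusted log-rank, the Kaplan–Meier curves and the restricted mean fallback as supportive analyses.

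The cost is wording and programming only, with no new data, visits or participants. There are two small downsides: the reported hazard ratio becomes conditional on the covariates, and missing baseline values need a simple, pre-specified imputation.

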### Safety review

The most frequent adverse events related to the oral use of NAC are gastrointestinal (nausea, vomiting, diarrhea, abdominal pain, nausea, stomatitis) [20]. NAC may have a detrimental effect on the stomach’s mucosa which may be relevant to patients with active peptic ulcers. Less frequent events that have been reported include anaphylactic shock, anaphylactoid reaction, bronchospasm, angioedema, dyspnea, tachycardia, rash, pruititis, and urticaria [21]. Headache, tinnitus, pyrexia, hypotension, facial edema and hemorrhage have also been reported with oral NAC. NAC has been shown to reduce platelet aggregation, although the clinical significance of this is unknown [22].

The PANORAMA study showed that IPF patients receiving both oral NAC and pirfenidone experienced higher rates of photosensitivity rash compared to those that received pirfenidone only (9% vs. 2%). However, these rates were markedly lower than the rates reported in pooled phase III trial data (33%), suggesting that this difference in the PANORAMA study may have been driven by its smaller sample size [23]. PANORAMA and a small study from Japan that examined the efficacy and tolerability of combination therapy with inhaled NAC and pirfenidone versus pirfenidone alone had findings that suggested more rapid disease progression in the group that received combination therapy [24]. The *TOLLIP* TT genotype of participants in both studies was unknown and has been shown to have a very low frequency among Japanese IPF patients. In addition, differences in dosage, modes of delivery for NAC and smaller sample sizes make the collective interpretation of these studies’ findings difficult [25].

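### The planned subgroup p-values, on their natural reading, test NAC within each level and not whether its effect differs between levels, and no interaction test is named.

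*Protocol article*

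**What the plan says.** The protocol article, under Analysis of the primary endpoint, places subgroup work among the secondary analyses and says the NAC effect will be explored there. The output is fixed as "results tabulated (estimated hazard ratio by subgroup, corresponding 95% confidence interval and p-value", together with forest plots.

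Ten factors are listed: concomitant therapy, sex, race/ethnicity, smoking history, age, baseline FVC in litres, baseline FVC in % predicted, baseline DLCO in absolute units, baseline DLCO in % predicted, and respiratory hospitalization in the previous year.

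The statistical sections name no treatment-by-subgroup interaction test. They do not say outright what the subgroup p-value tests, and they set no rule for declaring that an effect differs between subgroups.

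**The concern.** A p-value attached to each subgroup's hazard ratio answers whether NAC works in that level. A subgroup analysis is meant to ask whether the effect differs between levels, and only a contrast between the levels tests that. When events are few, each level is underpowered. One level can then reach p<0.05 and the other miss it although the effect is identical in both.

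In a positive trial, such a table invites the reading that some patients do not benefit. The trial's own premise was established by the right kind of test: the Rationale section reports a significant interaction between TOLLIP genotype and NAC. The subgroup plan does not carry that standard over. Analyses of the secondary time-to-event endpoints are to be similar to the primary one, so the same table could be repeated for endpoints with fewer events.

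**Working it through.** **Inputs from the protocol**
- Allocation: "Study participants will be randomized to NAC or placebo in a 1:1 fashion".
- Sample size and dropout: "Power estimates assume censorship/dropout rate of 10% for the NAC vs placebo comparison in 200 randomized participants".
- Placebo rate: "we conservatively estimate a placebo yearly event rate to be 24% for the primary composite endpoint in participants not taking concomitant therapy". For those on an antifibrotic, "The remaining 65% are assumed to have half the shown event rate in each arm".
- Effect: 66.7% reduction in the 12-month rate, so 24% to 8% without concomitant therapy and 12% to 4% with it.
- Follow-up: 24 months for all, exponential event times, log-rank test.

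**Step 1: event probabilities and hazard ratio.** The 24-month risk is 1 − (1 − yearly rate)².
- Placebo: 0.35 × (1 − 0.76²) + 0.65 × (1 − 0.88²) = 0.35 × 0.4224 + 0.65 × 0.2256 = 0.294.
- NAC: 0.35 × (1 − 0.92²) + 0.65 × (1 − 0.96²) = 0.35 × 0.1536 + 0.65 × 0.0784 = 0.105.
- Overall hazard ratio: ln(1 − 0.105) / ln(1 − 0.294) ≈ 0.317.

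**Step 2: reproduce the stated power.** The protocol states a sample size "which will provide 90.1% power assuming a two-sided type-I error rate of 0.05". With 90 evaluable per arm, a simulated log-rank test gives 90.4% and a two-proportion formula gives 89.6%. Freedman's formula with exponential 10% dropout gives 89.8%. The stated figure is reproduced. Schoenfeld's formula gives 93.1% and does not match.

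**Step 3: events (derived; the protocol gives no total).** 90 × (0.294 + 0.105) = 35.9 with 180 evaluable. About 38 result with exponential dropout, and 100 × 0.399 = 39.9 with none. Other rows of Table 3 give about 34 to 62.

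**Step 4: hand check of one factor under a uniform effect.** Take 38 events and hazard ratio 0.317. Power in a level with d events (Freedman) is Φ(√d × (1 − 0.317)/(1 + 0.317) − 1.96). If the levels have powers p₁ and p₂, the chance that exactly one is significant is p₁(1 − p₂) + p₂(1 − p₁).
- Even split of events, 19 and 19: power 0.618 each, so 2 × 0.618 × 0.382 = 0.47. Schoenfeld's formula gives 0.706 each, so 0.415.
- 85/15 split, 32.3 and 5.7 events: powers 0.838 and 0.235, so 0.838 × 0.765 + 0.235 × 0.162 = 0.68.

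**Step 5: simulation.** There were 3,000 trials of 200 participants per scenario, with ten independent two-level factors and the same relative reduction in every subgroup. Each level was tested by log-rank, and each factor by an interaction z-test on (O − E)/V. The 65% on concomitant therapy is from the protocol. The other shares (50% to 85%, one factor at 15%) are assumed.

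| True reduction | Mean events | Levels split at p=0.05, per factor | Any of 10 split | Interaction p<0.05, per factor | Any of 10 |
|---|---|---|---|---|---|
| 66.7% | 38 | 44–70% | 97% | 3–4% | 27% |
| 50% | 43 | 47–57% | 90% | about 4% | 34% |
| None | 56 | 8–9% | 41% | about 5% | 41% |

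The hand check brackets or comes close to the simulated per-factor values: 0.415 to 0.47 against 0.44–0.45 for 50% shares, and 0.68 against 0.70 for the 85/15 factors. The no-effect figures also agree with theory: 2 × 0.05 × 0.95 = 9.5% per factor for a split, and 1 − 0.95¹⁰ = 40% for any of ten interaction tests.

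**The case against.** The strongest reply is that the article only says effects will be explored, with confidence intervals and forest plots, and prescribes no inference from the p-values. It also condenses a longer plan, and an interaction test may stand in an analysis plan that is not shown. The first part stands: a reader might infer that subgroup differences will be judged by within-level significance in place of interaction, but no rule says so and no text excludes an interaction test. The second part stands only in part, because the article does not merely stay silent. It names the statistic to be tabulated, and on its natural reading that statistic does not address heterogeneity.

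A reader might also infer that spurious differences are almost guaranteed. The 97% figure does not support that in general. It needs a true effect near the design value and a reader who treats a split in significance as a difference. It also needs independent factors, whereas FVC and DLCO each appear twice in correlated forms, so the any-of-ten figures are somewhat high. Correlation between factors does not alter the per-factor figures. With no effect, ten interaction tests mislead as often as the planned table does.

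A third tempting reading is that the plan hides a pirfenidone-specific problem. The Safety review section does report "findings that suggested more rapid disease progression in the group that received combination therapy". It also says those studies are hard to interpret together, because genotype was unknown, dose and route differed, and samples were small. The pooled definition, "concomitant therapy (pirfenidone or nintedanib vs. none", belongs to the adjustment variable. The levels of the concomitant-therapy subgroup are not stated. The point therefore does not rest on pirfenidone.

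**Conclusion.** The point holds as a defect in the stated subgroup output. The p-value described does not test whether the NAC effect differs between levels, and no test that does is named. If NAC works uniformly at the design effect, a given factor would show a split in significance in roughly 44–70% of trials, against about 3–4% false signals from an interaction test. These figures rest on the protocol's event rates, on about 38 events (36 to 40 depending on how dropout is handled), and on subgroup shares that are assumed except for concomitant therapy. With no true effect, neither approach has an advantage across ten factors. The primary log-rank test, its type I error, its power and the sample size are unaffected.

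**What to change.** In Analysis of the primary endpoint, replace the per-level p-values with one treatment-by-subgroup interaction p-value per factor. Keep the subgroup hazard ratios with 95% confidence intervals in the table and forest plot. State that the results are exploratory and unadjusted for multiplicity.

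Optionally, show pirfenidone and nintedanib users descriptively as separate rows of the concomitant-therapy subgroup. The base-case rates imply few events there: 65 × (0.2256 + 0.0784) ≈ 20 across both drugs and both arms, before dropout.

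The change costs a sentence and revised table shells, with no new data, participants or alpha. Its downside is that interaction tests have little power at this event count, so most will be inconclusive. The confidence intervals will show that directly.
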